### Outcome measures

#### Primary study parameter/end point

The primary objective of this study will be to quantify pain or functional improvement using the American Orthopaedic Foot and Ankle Society (AOFAS) score at 26 weeks follow-up. Studies evaluating the efficacy of PRP in knee OA maintained a follow-up between 3 and 12 months. We therefore opted to take 26 weeks for our primary outcome measure.^10^ The AOFAS is a validated scale for ankle OA (0–100) measuring three subdomains (pain, function and alignment), which together total nine items.^20–23^ The subdomain of pain is measured by one item where a maximal score of 40 indicates no pain. Function consists of 7 items where full function is indicated by the maximal score of 50 points. Similar to the pain subdomain, alignment has a potential maximum score of 10 points using one item, indicating good alignment.^20 21^ The AOFAS questionnaire, having undergone forward and backward translation to Dutch by de Boer *et al*, has an excellent internal consistency (Cronbach’s α=0.947) and an excellent test–retest reliability (Intraclaas Correlation Coefficient 0.93).^20^

### Secondary study parameters/end points

Secondary outcome measures are a number of other PROMs. Specific time points of the secondary outcome measures can be found in table 1.

Ankle Osteoarthritis Score (AOS) is a Visual Analogue Scale (VAS) from 0 to 100 mm with 18 questions; 9 relating to pain and 9 relating to disability.Foot and Ankle Outcome Score (FAOS): each question is assigned 0–4 points based on the answer given. The scale runs from 0 (extreme symptoms) to 100 points (no symptoms).In order to evaluate pain, the pain subscale of AOFAS (0–40 points) will be analysed. On this scale, the lower the score the more pain the patient has. Additionally, a VAS score (VAS 0–100 mm) is measured during activities of daily living, with 0 mm being no pain and 100 mm the worst pain imaginable.Total AOFAS score at the other time points than the primary one (at 6, 12 and 52 weeks as well as 5 years).Ankle Activity Score (0–10 points) is scored according to chart based on the performable activity levelSubjective patient satisfaction (four categories): poor, fair, good, excellent.Short Form Health Survey-36 is a health-related quality of life score (0–100 points). The higher the patient scores, the higher the disability.The Global Attainment Scaling is a method of scoring based on achievement related to predetermined goals in agreement with the patient. Points are subtracted for not achieving the predefined goals or vice versa. Scores range from 100 (high functioning) to 0 (severely impaired)EuroQol-5 dimensions-3 levels (EQ-5D-3L) utility score allows a patient’s health to be defined by a 5-digit number.PRODISQ will be used to determine indirect costs and direct costs cost-effectivity. PRODISQ is taken at baseline and every 3 months thereafter up until 1 year. This will be done in conjunction with the EQ-5D-3L.

### Loss to follow-up

The coordinating researcher will attempt to limit loss to follow-up as much as possible by contacting every patient and being present at every patient visit. All digital questionnaires will be constantly monitored to ensure they are being filled in and otherwise followed up by the coordinating researcher. In the event of patient withdrawal, an analysis of demographic and prognostic characteristics will be done on these cases and the remaining patients. As previously described by Järvinen *et al*, we will document the patient eligible for and compliant with each follow-up.^24^

### Missing items

Missing items of a score will be handled according to the instructions of the specific scales. In the event of no instructions, we will calculate the percentage of missing items on a scale. Due to the potential impact on trial conclusions, multiple imputation (if >10% missing items on a scale) will be applied.

### Sample size

Based on previous and ongoing studies, the study protocol of the RCT is designed to detect a difference of 12 points (0–100) on the AOFAS score. There is no official agreement on the minimal clinical important difference for the AOFAS score regarding ankle OA. However in relatable musculoskeletal literature, 10%–15% of the used scale was reported.^13 25 26^ Our predefined minimal clinical important difference of 12% is located within this range.^13 25 26^ Based on a previous placebo-controlled RCT on injection therapy (hyaluronic acid) in ankle OA by De Groot *et al*, an SD of 16.3 can be expected.^6^ Taking into account a two-sided level of significance of 5%, a power of 90% and a dropout rate of 10%, approximately 50 (45 plus 10% drop out) patients per group will be needed (n=100 in total).

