### Replacement of individual patients after withdrawal

In the sample size calculation, we compensated for an expected loss of 10% of patients to follow-up. No patients will be replaced after withdrawal.

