### Primary outcome measure

Analysis will be performed using an intention-to-treat approach. To test for the effect of treatment on the between-group difference in primary outcome, we will use a repeated measurement general linear model. Changes from baseline to all follow-up time points will be included in the model. Adjustments will be made for those baseline variables that influenced the primary outcome with p<0.10.

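### The stated inputs require 39 to 40 evaluable patients per group for 90% power, not 45; the 10% dropout allowance appears to have been added twice.

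*Protocol article*

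**What the plan says.** The Sample size section of the protocol article gives a full set of planning inputs. The trial is "designed to detect a difference of 12 points (0–100) on the AOFAS score", and from an earlier placebo-controlled injection trial in ankle osteoarthritis "an SD of 16.3 can be expected". The error rates and attrition are "a two-sided level of significance of 5%, a power of 90% and a dropout rate of 10" per cent. The result is given as "approximately 50 (45 plus 10% drop out) patients per group will be needed (n=100 in total").

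The section on replacement of patients after withdrawal agrees that there is one attrition allowance: "we compensated for an expected loss of 10% of patients to follow-up". Neither section mentions a correlation between visits, a rank-test correction, a multiplicity adjustment or any other allowance.

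**The concern.** The parenthesis makes 45 the evaluable number and 50 the number after dropout. If so, 45 per group should follow from the difference, SD, significance level and power alone. It does not; it is 5 to 6 patients per group too high, which is more than rounding. The word "approximately" qualifies the 50, not the 45.

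Two things depend on this. First, the article says 100 patients are needed, and on its own inputs about 90 are. The other 10 or so people enter a placebo-controlled trial with repeated blood draws and joint injections without a stated reason. Second, power is the yardstick for a null result. The Discussion says a negative outcome would prevent wide use of the treatment, so readers will want to know how sensitive the trial was, and the printed 90% at 12 points does not describe 45 evaluable patients per group.

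**Working it through.** **Inputs**, all from the Sample size section: difference δ = 12, SD σ = 16.3, two-sided α = 0.05, power 0.90, dropout 10%, two equal groups.

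**Step 1. Attempt to reproduce 45.** Normal approximation:

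n per group = 2 × (z₀.₉₇₅ + z₀.₉₀)² × (σ/δ)² = 2 × (1.960 + 1.2816)² × (16.3/12)² = 38.8, so 39.

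The t distribution needs slightly more. Noncentral-t power is 89.4% at 39 and 90.2% at 40, so 40 per group. The stated 45 is not reproduced.

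**Step 2. Does a common variant give 45?** Same difference and SD:

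| Variant | n per group (normal / t) |
|---|---|
| Two-sided 5%, 80% power | 29 / 30 |
| Two-sided 5%, 85% power | 34 / 35 |
| Two-sided 5%, 90% power | 39 / 40 |
| Two-sided 5%, 95% power | 48 / 49 |
| One-sided 5%, 90% power | 32 / 33 |
| Two-sided 2.5%, 90% power | 46 / 48 |

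None gives 45.

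**Step 3. Dropout.**

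- Once: 40 / 0.9 = 44.4, rounded up to 45. Starting from 39: 39 / 0.9 = 43.3, rounded up to 44. The total randomised is therefore 88 to 90.
- Twice: 45 / 0.9 = 50. (Adding 10% gives 45 × 1.1 = 49.5, also 50.)

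The chain 40 → 45 → 50 matches both printed numbers.

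**Step 4. What 45 and 50 per group provide.** The noncentrality at 45 is 12 / (16.3 × √(2/45)) = 3.49.

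| Evaluable per group | Power, normal | Power, t |
|---|---|---|
| 40 | 90.9% | 90.2% |
| 45 | 93.7% | 93.2% |
| 50 | 95.7% | 95.4% |

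**Step 5. What would make 45 correct at 90% power (t-test)?** Either a difference of about 11.3 points at SD 16.3, or an SD of about 17.4 at 12 points (solved value 17.37; 17.4 itself gives 89.9%). The article states neither.

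**The case against.** **The cause of the 45 is not established.** This is correct. A worst-case rank-test correction applied to the normal-approximation figure gives 38.8 / 0.864 = 44.9, also 45. The full protocol behind the article might record that or another allowance. But the mismatch does not depend on its cause. The article prints a complete set of inputs and attributes the result to them, so if a further allowance was used, the sentence is incomplete in a way that makes it wrong.

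**The discrepancy is conservative.** This also stands. With 45 evaluable per group the 90% target is met, and the trial is not underpowered on its stated inputs. A reader using 90% would slightly understate how informative a null result is. What remains is a main planning figure that cannot be reproduced and about 10 patients without a stated justification.

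**The 93% belongs to a simple t-test.** The primary analysis is different: "we will use a repeated measurement general linear model", applied to changes from baseline with baseline adjustment. The article does not say whether 16.3 is the SD of a score or of a change. Assuming it is a single-visit SD, the SD of a change is 16.3 × √(2(1 − ρ)). A comparison of changes with 45 per group then has about 83% power at a baseline correlation ρ of 0.3, 93% at 0.5 and 99% at 0.7. This does not rescue the 45, because the Sample size section uses no correlation, but any corrected power statement should name the test and SD it refers to.

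**The withdrawal section is not a second error.** Agreed. It confirms that one 10% allowance was intended and contains no mistake of its own.

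**Conclusion.** The concern holds. For a two-sample comparison on the stated inputs, 90% power needs 39 (normal) or 40 (t) evaluable patients per group, and 44 or 45 randomised per group after one 10% dropout allowance. The article's 45 evaluable and 50 randomised exceed this by 5 to 6 per group, or 10 to 12 randomised patients in total. At 45 evaluable per group the power is about 93%, and with no dropout at all about 95%. That the sentence does not follow from its inputs is certain; double-counted dropout is the most natural explanation but remains an inference. The power figures assume an unadjusted two-sample t-test with SD 16.3. The error leaves the trial with more power than stated, so it calls for a correction of the text and does not threaten the design.

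**What to change.** Keep the 100 patients and rewrite the result of the calculation, for example: 'For a two-sample t-test with SD 16.3, 40 evaluable patients per group give 90% power to detect 12 points, which is 45 randomised per group allowing for 10% dropout. We will randomise 50 per group. With 45 evaluable, power is 93% for 12 points, or 90% for 11.3 points or for an SD of about 17.4.'

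If the 45 came from a deliberate allowance, such as a larger SD, a rank-based test or covariate adjustment, state that allowance and show that it leads to 45. In either case, say whether 16.3 is the SD of a score or of a change.

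The cost is a wording correction. Recruitment, conduct and analysis do not change.

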### Data management

After giving permission for participating in this study, patients will receive a link to fill in digital surveys. All data gained outside Castor EDC will be stored on the AMC secured hard drive. All data will be coded and stored in the Castor EDC online database, which meets the AMC safety criteria and GCP guidelines. The primary investigator and project leader will safeguard the coded data through password secured access. All patient’s data will be archived for at least 15 years and handled with in accordance with the Dutch Personal Data Protection Act (Wbp). Data protection is provided through the safety protocol of Castor EDC with automated backups and Secure Sockets Layer (SSL) security.

### Statistical analysis

A standard operating procedure will be available to logically recode and clean the data. The data will be interpreted according to a blinded data interpretation scheme described by Järvinen *et al*.^24^ A statistical expert (SB) is present among the authors. The authors will interpret the statistical results until a consensus is reached. Once the authors are in agreement, the two groups will be unblinded and no changes will be made to the interpretation of the results.

### Baseline characteristics

Baseline characteristics will be analysed between groups using descriptive statistics.

### Primary outcome measure

Analysis will be performed using an intention-to-treat approach. To test for the effect of treatment on the between-group difference in primary outcome, we will use a repeated measurement general linear model. Changes from baseline to all follow-up time points will be included in the model. Adjustments will be made for those baseline variables that influenced the primary outcome with p<0.10.

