### Study design

The Platelet-Rich plasma Injection Management for Ankle OA (PRIMA) study is a multicentre, stratified, block‐randomised, double‐blind, placebo‐controlled trial design will be conducted in order to compare two treatment groups: PRP versus placebo (saline). After the 26 weeks follow-up of the last patient in the study, the principal investigator and coordinating researcher will be unblinded only after the analysis of the primary outcome. A flow chart of the design and follow-up is shown in figure 1. The study included its first patient in August 2018 and aims to include the last patient by January 2021, consequently allowing analysis and then deblinding to commence after the last follow-up (26 weeks) of the last patient by July 2021.

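### The primary model, read conventionally, drops patients with a missed visit and spans visits not yet reached at the week-26 analysis, which sits badly with the stated intention-to-treat approach

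*Protocol article*

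**What the plan says.** All places are in the protocol article.

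- **Primary outcome measure (statistical analysis).** The principle is "Analysis will be performed using an intention-to-treat approach". For the between-group test, "we will use a repeated measurement general linear model". On the visits: "Changes from baseline to all follow-up time points will be included in the model". No estimation method is named, and nothing is said about a patient who lacks one of the change scores.
- **Secondary study parameters/end points.** The AOFAS visits besides week 26 are listed: "Total AOFAS score at the other time points than the primary one (at 6, 12 and 52 weeks as well as 5 years".
- **Study design.** The primary analysis is timed at week 26 of the last patient, "allowing analysis and then deblinding to commence after the last follow-up (26 weeks) of the last patient by July 2021". The first patient entered in August 2018 and the last is expected by January 2021.
- **Missing items.** First, "Missing items of a score will be handled according to the instructions of the specific scales". Where a scale gives no instructions, "multiple imputation (if >10% missing items on a scale) will be applied".
- **Loss to follow-up.** For withdrawals, the analysis promised is descriptive: "an analysis of demographic and prognostic characteristics will be done on these cases and the remaining patients".
- **Replacement of individual patients after withdrawal; Sample size.** A 10% loss is expected, withdrawn patients are not replaced, and 45 evaluable patients per group become 50 enrolled.

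**The concern.** Three statements do not fit together.

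The model's name conventionally means repeated-measures ANOVA or MANOVA, with one row per patient and one column per visit. A row with an empty cell is deleted, so a patient who skipped week 12 but attended week 26 would not contribute to the week-26 comparison.

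The imputation rule that might fill such a cell is written for gaps inside a questionnaire. Withdrawal has its own section, which gives no rule for bringing those patients into the model.

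The visits to be modelled extend beyond the date at which the primary analysis is run.

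If missed visits are related to how the patient is doing, a comparison among complete patients is no longer a comparison of the randomised groups. That is what the intention-to-treat commitment is meant to protect.

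**Working it through.** **1. The plan's own sample size.** Inputs from Sample size: difference 12, SD 16.3, two-sided 5%, power 90%, dropout 10%.

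- n per group = 2 × [16.3 × (1.960 + 1.282) / 12]² = 38.8, so 39. The exact t calculation needs 40.
- The stated 45 is not reproduced. The step from 45 to 50 is: 45 / 0.9 = 50.
- With 45 per group, noncentrality is 12 / (16.3 × √(2/45)) = 3.49 on 88 degrees of freedom, and power is 93%.

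The discrepancy is conservative and separate from this point. It matters here only because it leaves some slack in power.

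**2. Visits available at the primary analysis.** AOFAS follow-up is at 6, 12, 26 and 52 weeks and 5 years. The analysis is due in July 2021.

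- 5 years: the first patient entered in August 2018 and reaches 5 years in August 2023. Nobody has this value, so a complete-row model over all five visits would contain no patients.
- 52 weeks: patients enrolled in about the last 6 months of accrual have not reached it. Assuming uniform accrual over about 30 months, 6/30 × 100 = 20 patients, leaving about 40 per arm before any visit is missed.
- 6, 12 and 26 weeks: due for everyone. Three is therefore the relevant visit count.

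**3. Patients left under row deletion, three visits.** The missingness rates m are assumptions, since the article gives only the overall 10% loss. Retained per arm = 50 × (1 − m)³. Power is from the noncentral t for 12 points with SD 16.3, with n rounded down.

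| Assumption | Retained per arm | Power |
|---|---|---|
| 3% per visit, independent | 50 × 0.97³ = 45.6 | 93% |
| 5% per visit, independent | 50 × 0.95³ = 42.9 | 92% |
| 10% per visit, independent | 50 × 0.90³ = 36.5 | 87% |
| The same 10% miss all later visits | 45 | 93% |

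The 10% independent case makes 1 − 0.729 = 27% of patients incomplete, well above the loss the plan allows for.

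**4. Bias, by illustration.** A large simulation was run under assumed conditions:

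- correlation 0.6 between visits, and true effects of 6, 9 and 12 points at 6, 12 and 26 weeks;
- dropout after week 6 by half of the patients in the lowest fifth of week-6 change. This gave 12.6% dropout on placebo and 7.3% on PRP.

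Complete patients gave a week-26 difference of 11.4 against the true 12. A method valid under missing at random, using everyone's week-6 data, gave 12.0. The 0.6-point shift is towards no effect here. Its size and direction depend on the assumed dropout pattern.

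**5. Scope of the item rule.** AOFAS has nine items (Primary study parameter/end point), so one blank is 1/9 = 11% and already exceeds the 10% trigger. That suits gaps within a completed questionnaire. Nothing in the section refers to a visit or a withdrawn patient.

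**The case against.** A reader might infer that the plan is a complete-case analysis. The article never says so. It names a model without an estimation method, and the label is also used loosely for linear mixed models, which keep patients with partial data. The intention-to-treat sentence opens the same section, so a reading consistent with it is open. This stands: row deletion is the conventional meaning of the label, not a stated rule.

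A reader might also infer that missed visits are certainly not imputed. A wholly missed questionnaire has 100% of its items missing and literally meets the trigger. If that is intended, the rows are filled and nobody is deleted. The section heading and the separate section on withdrawal make this doubtful, but do not exclude it.

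Intention-to-treat first means analysing patients in the group to which they were randomised; how missing outcomes are handled is a related but separate choice. So there is a tension under one reading of the model, not a flat contradiction.

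Detailed missing-data rules and any sphericity correction commonly sit in an analysis plan, which is not shown. No criticism of sphericity is made: the article is silent on it, and a group contrast at a single visit does not depend on it.

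Finally, a reader might infer a serious loss of power by counting four or five visits. Those counts do not fit an analysis run at week 26, and with three visits the loss is modest.

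What the objection leaves standing is the mismatch between the model as named, its visit list and the analysis date. All three are in the text.

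**Conclusion.** The point holds in limited form. As conventionally read, the named model would drop patients with a recorded 26-week score because another visit is missing, and the item-level rule does not clearly prevent that. Independently of that reading, the visit list cannot be applied literally at the planned analysis date, because 5-year data exist for nobody and 52-week data are missing for about 20 of 100 under uniform accrual.

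Power is the lesser matter. It stays at about 92% to 93% in three of the four assumed patterns and falls to 87% only with 10% independent missingness at each of three visits. The greater risk is bias and departure from the intention-to-treat principle if missed visits relate to response. The 0.6-point shift in the illustration shows that this can happen; it does not predict its size in this trial.

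**What to change.** In the primary outcome analysis section:

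- Replace the model by a likelihood-based linear mixed model for repeated measures on 6, 12 and 26 weeks, for example REML with unstructured covariance. Include every randomised patient with at least one post-baseline score, analysed as randomised, and make the week-26 group contrast the primary estimate. If a mixed model was meant all along, saying so and naming the visits is enough.
- Analyse 52 weeks and 5 years later, as secondary outcomes, once those visits are complete.
- Keep the missing-items rule for scoring questionnaires, and say that it does not govern missed visits.
- Add one sensitivity analysis for missing 26-week scores, such as multiple imputation at score level with a delta shift. It can also take in patients with no post-baseline score, whom the mixed model leaves out.

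Score-level multiple imputation combined with the named model would also retain all patients, provided the visits are limited to week 26.

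The cost is a few sentences and minor programming. No new data are needed.

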**Methods and analysis:**

We will conduct the Platelet-Rich plasma Injection Management for Ankle OA study: a multicentre, randomised, placebo-controlled trial. One hundred patients suffering from ankle OA will be randomised into two treatment groups: PRP injection or placebo (saline) injection. Both groups will receive two injections of PRP or placebo at an interval of 6 weeks. Primary outcome is the American Orthopaedic Foot and Ankle Society score at 26 weeks. Secondary outcomes determined at several follow-up moments up to 5 years, include Ankle Osteoarthritis Score, Foot and Ankle Outcome Score, pain subscale of (0–40), Visual Analogue Scale score (0–100), Ankle Activity Score (0–10), subjective patient satisfaction Short Form Health Survey-36, Global Attainment Scaling and the EuroQol-5 dimensions-3 levels utility score. A cost-effectiveness analysis will be performed at 1 year.

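### AOFAS at 26 weeks is the primary endpoint, but the primary model takes in every follow-up visit and the text does not fix which of its tests is primary

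*Protocol article*

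**What the plan says.** **Endpoint.** The abstract (Methods and analysis) states: "Primary outcome is the American Orthopaedic Foot and Ankle Society score at 26 weeks". The section Primary study parameter/end point agrees: pain or functional improvement is to be quantified "using the American Orthopaedic Foot and Ankle Society (AOFAS) score at 26 weeks follow-up". The list of secondary endpoints contains "Total AOFAS score at the other time points than the primary one (at 6, 12 and 52 weeks as well as 5 years".

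**Model.** Under Statistical analysis, Primary outcome measure, the aim is given as "To test for the effect of treatment on the between-group difference in primary outcome", and for this "we will use a repeated measurement general linear model". The next sentence is "Changes from baseline to all follow-up time points will be included in the model". The section on secondary outcome measures uses the same model and the same sentence.

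**Timing.** Under Study design, "The study included its first patient in August 2018", the last inclusion is aimed for by January 2021, and the calendar is described as "allowing analysis and then deblinding to commence after the last follow-up (26 weeks) of the last patient by July 2021". That section and the section on randomisation and blinding both allow the principal investigator and coordinating researcher to be unblinded only once the primary outcome has been analysed.

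**The concern.** The endpoint is one time point; the model that is meant to test it contains five. Four of those five AOFAS values are classed elsewhere in the article as secondary. A repeated-measures general linear model yields several tests of treatment: the group effect averaged over visits, the group-by-time interaction, and a contrast at any one visit. The article does not fix which of these is the primary test.

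This matters because the three tests need not agree. The averaged effect equals the 26-week difference only if the treatment effect is the same at every visit. The interaction asks whether the difference changes over time, which is not an efficacy question. A constant effect cannot be taken for granted here: the second injection is given at the 6-week visit, so the 6-week value cannot reflect the full two-injection course.

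The inclusion of every follow-up visit also clashes with the calendar. The primary analysis is due when the last patient reaches 26 weeks, before the later visits are complete.

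**Working it through.** **1. The plan's own sample-size figure.** Inputs from the Sample size section: difference 12, SD 16.3, two-sided 5%, power 90%, dropout 10%, giving 45 per group before and 50 after dropout.

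- n per arm = 2 × (1.960 + 1.282)² × 16.3² / 12² = 38.8, so 39 (40 with the t distribution).
- The stated 45 before dropout is therefore not reproduced; only the step 45 / 0.9 = 50 is. The difference is on the safe side and is separate from this point.
- The inputs are those of a two-group comparison of means at one time point. No within-patient correlation appears, as a test averaged over visits would need.

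The stated 45 evaluable patients per arm are used below.

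**2. Calendar.**

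- Last inclusion January 2021 + 26 weeks = July 2021, as stated.
- Last 52-week visit: between about the end of December 2021 and the end of January 2022.
- First 5-year visit: August 2018 + 5 years = August 2023. Last: January 2026.
- Assuming even recruitment from August 2018 to January 2021, about 79% to 80% of patients could have a 52-week AOFAS in July 2021, and none a 5-year AOFAS.

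A complete-case fit on all five follow-up visits would have no usable patients in July 2021. One on visits up to 52 weeks would lose about 20% of patients before any dropout.

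**3. Averaged test against the 26-week contrast.** Only visits that will be complete in July 2021 are used (6, 12 and 26 weeks). Assumptions, not in the article: SD 16.3 for the analysed value at each visit, a common correlation ρ between visits of 0.5 (range 0.3 to 0.7), and the effect profiles themselves.

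- SD of the mean of k visits = 16.3 × √[(1 + (k − 1)ρ) / k]. For k = 3 and ρ = 0.5: 16.3 × √(2/3) = 13.3.
- Standard error of the group difference = SD × √(2/45): 2.81 for the three-visit average, 3.44 for a single visit.
- Noncentrality = true difference / standard error; power from the noncentral t distribution with 88 degrees of freedom.

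| True difference at 6/12/26 weeks | Average | Averaged test, ρ = 0.5 (ρ = 0.7 to 0.3) | 26-week contrast |
|---|---|---|---|
| 4/8/12 | 8 | 8 / 2.81 = 2.85: 81% (73% to 88%) | 12 / 3.44 = 3.49: 93% |
| 12/8/4 | 8 | 2.85: 81% (73% to 88%) | 4 / 3.44 = 1.16: 21% |
| 12/12/12 | 12 | 12 / 2.81 = 4.28: 99% (97% to 99.7%) | 3.49: 93% |

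The first two rows have the same average, so the averaged test cannot tell an effect that builds to the design value at 26 weeks from one that has faded to a third of it.

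**The case against.** The strongest reply is that the article aims the test at the primary outcome, and the primary outcome is defined at 26 weeks. On that reading the other visits only serve as repeated measures, and the 26-week contrast is taken from the model, which is a standard approach. Nowhere does the article say that the test is averaged over visits. Model terms and contrasts are also commonly left to a statistical analysis plan, which is not shown here.

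Most of this stands. A reader might infer that the primary analysis answers a different question from the endpoint; the article does not support that, because the 26-week contrast is a possible reading. The missing contrast alone would be no finding. What does not fall away is the stated rule that all follow-up time points enter the primary model. That is not missing detail: it conflicts with the article's own calendar and draws the visits it calls secondary into the primary analysis. An analysis plan limited to 26 weeks would have to depart from it.

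Two further inferences are tempting and also go too far:

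- **That the analysis cannot be run in July 2021.** This is so only for a model that must contain complete data at every visit. A model limited to visits up to 26 weeks, or a likelihood-based mixed model on the data available by then, could be fitted. The article states neither.
- **That the primary result would be refitted after unblinding.** No refit is planned, and the Statistical analysis section rules out changing the interpretation once the groups are unblinded.

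It is also fair to say that the effect profiles are illustrative and that averaging gains power when the effect is constant. The last row of the table shows this.

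**Conclusion.** The point holds as a conflict and an ambiguity in stated text. The endpoint is AOFAS at 26 weeks; the primary model is said to contain all follow-up visits; the article does not settle which test is primary; and the literal wording does not fit an analysis due by July 2021, when roughly a fifth of patients would lack a 52-week value (assuming even recruitment) and all would lack a 5-year value.

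The consequence is conditional. Only if the overall treatment effect were used as the primary test would power for a 12-point difference at 26 weeks move from 93% to about 81% under a 4/8/12 profile, or to about 99% under a flat one, and only then would a fading 12/8/4 effect be declared significant in 81% of trials against 21% at 26 weeks. These figures rest on 45 evaluable patients per arm, a constant SD of 16.3, a common correlation of 0.5 and assumed profiles. The calendar conflict needs none of these power assumptions.

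**What to change.** In the section on the primary outcome analysis, or in the statistical analysis plan with a matching correction to the protocol, state before unblinding that:

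- the primary model contains the AOFAS values at 6, 12 and 26 weeks only, with treatment, visit and treatment-by-visit terms;
- the single primary test and estimate is the treatment difference at 26 weeks, with its 95% CI;
- AOFAS at 52 weeks and 5 years is analysed in a separate secondary model that does not alter the primary result.

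The cost is two or three sentences and no new data. The one statistical price is some power if the effect is constant over time: 93% for the 26-week contrast against about 99% for the three-visit average in the example above. That is still above the planned 90%.
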